## Abstract

**Background:**

Mastectomy currently constitutes a necessary surgical procedure in the oncologic setting and in the context of high risk. Prepectoral breast reconstruction (PBR) has been proposed as a surgical alternative to retropectoral techniques by providing less postoperative morbidity and a better cosmetic result. However, there is a lack of prospective studies that have evaluated its safety and patient-reported satisfaction.

**Methods:**

We conducted a prospective cohort study to assess the safety, quality of life and cosmetic sequelae of PBR in women with breast cancer and high risk. The study’s main objective is to assess the safety of PBR in terms of postsurgical complications and the feasibility of reconstruction (loss of implants). The secondary objectives are to evaluate oncologic safety (local relapses, residual glandular tissue) and to identify factors related to quality of life and cosmetic sequelae. The evaluation of residual tissue will be conducted by MRI 12 to 18 months after the surgery, and the quality-of-life assessment will be performed using the Breast-Q questionnaire. An initial patient evaluation will be conducted 12–18 months after the surgery, and a second evaluation will be performed at 5 years. The estimated sample size is 81 patients.

**Discussion:**

The PreQ-20 study will analyze the impact of PBR on 3 separate measures: safety, quality of life and cosmetic sequelae. Unlike other studies that analyzed these three measures jointly for women with breast cancer and high risk, this study will individualize the results for these 2 patient groups. This differentiation is necessary from the methodological point of view, given that the 2 patient groups have separate clinical and emotional implications. The assessment of these groups will focus on the following aspects: postoperative complications, local relapses, evaluation of residual glandular tissue and incidence rate of primary tumors in the same, the cosmetic sequelae and the satisfaction and the quality-of-life assessment by the patients.

**Trial registration:**

ClinicalTrials.gov: NCT04642508.

## Background

In recent years, mastectomy techniques have evolved towards less aggressive procedures with increased skin preservation, skin-sparing mastectomy (SSM), and skin and nipple-sparing mastectomy (NSM). Reconstructive procedures have changed the placement of implants from the retropectoral position towards the prepectoral location in an attempt to decrease postoperative pain, prevent animation deformity and improve the refilling of the lower pole. Various studies [1–3] published in the past 5 years have shown that the combination of SSM/NSM and prepectoral breast reconstruction (PBR) ensures good results both in the oncologic context and in reducing risk (RR). The meta-analysis by Li et al. [4] analyzed 16 studies that compared retropectoral breast reconstruction (RBP) with PBR and found no significant differences in the safety of the two procedures (in terms of seroma, implant loss, infection, skin necrosis), although PBR showed a lower incidence of capsular contracture, less pain and higher scores on the Breast-Q questionnaire compared with RBP.

Despite these technical improvements, there are still a number of unknowns regarding various clinical aspects related to PBR such as safety, quality of life and the progression of the cosmetic results. First, from the point of view of safety, the rate of postoperative complications needs to be evaluated, as well as local relapses in patients with breast cancer and primary tumors in women with high risk. There are some studies [5] that have analyzed this aspect, however, the level of evidence for these studies was low. Another aspect related to the safety of SSM and NSM is the presence of residual glandular tissue (RGT) because it can facilitate a local relapse in patients with breast cancer or promote the onset of a primary carcinoma, both in patients with cancer and those at high risk. Various studies have analyzed the presence of RGT after mastectomy [6–16]. None of these studies have reported the rate of RGT or the time interval between mastectomy and the MRI study. The identification of this RGT during follow-up facilitates the joint decision-making process with the patient, either for their specific follow-up or extirpation.

The patient-reported satisfaction and quality of life after PBR have been analyzed by several authors; however, only 3 studies have evaluated them prospectively [17–19]. The main limitations of these studies are the lack of differentiation in the results between patients with breast cancer and RRM, the scarce follow-up and the absence of a preoperative assessment in one of the studies [19]. Most of the women with breast reconstruction experienced changes and deterioration of their breast during the follow-up. There are no available prospective studies that have analyzed these changes during the follow-up for RBP or PBR. Some retrospective studies detect a very low incidence of complications, cosmetic deterioration and replacement of implants [20, 21]. In contrast, prospective studies have detected a higher rate of cosmetic sequelae after PBR [18, 19]. These studies highlighted the low breast satisfaction of patients with rippling, especially those who underwent a prepectoral procedure.

Although at this time SSM/NSM with PBR constitutes a necessary surgical procedure in the oncologic setting and in the context of high risk, there is a lack of prospective studies that have evaluated their oncologic safety and patient-reported quality of life. Therefore, the objective of this study will be to assess prospectively and with long-term follow-up the safety of sparing mastectomies with PBR. To do this, we will analyze the safety of the technique in terms of implant loss, polyurethane safety, and surgical complications; oncological safety in terms of RGT, local relapses and new tumors; and the resilience of the reconstruction, assessing cosmetic deterioration, the need for new surgeries and long-term patient satisfaction.

### Research hypothesis

Prepectoral breast reconstruction with polyurethane implant after mastectomy is a safe procedure.

### Study objectives

#### Main objective

To evaluate the safety of prepectoral reconstruction in terms of postsurgical complications and the feasibility of reconstruction (implant loss).

Secondary objectives:

To evaluate the safety of sparing mastectomy through the identification of RGT, primary carcinomas and breast cancer relapses (patients operated on for breast cancer).To assess satisfaction and quality of life after prepectoral reconstruction in women with breast cancer and those with high risk.To identify factors related to satisfaction and quality of life after prepectoral reconstruction.To evaluate the cosmetic sequelae after prepectoral reconstruction in women with breast cancer and with high risk.To identify factors related to the cosmetic sequelae after prepectoral reconstruction.

### Study design

Prospective single arm cohort study to evaluate the safety, quality of life and cosmetic sequelae of breast reconstruction using prepectoral implantation in women with breast cancer and those at high risk. The safety of the technique is assessed in terms of loss of implants.

## Methods

### Study setting

The study will be conduct in the Breast Unit of the University Hospital Complex of A Coruña, Spain.

### Exclusion criteria

The following clinical conditions were excluded from the study:

Inability to undergo magnetic resonance imaging during the diagnosis and follow-up.Inability to fill out the BREAST-Q questionnaire.Unwillingness by the patient to participate in the study.Breast sarcomas.PBR using expanders.Prepectoral reconstruction with mesh

### Interventions

#### Mastectomy technique

The breast removal will be performed using a mastectomy adapted to the breast and optimizing the preservation of the breast’s original elements (inframammary fold, skin envelope, fat transitions, nipple-areolar complex) according to each patient’s anatomical and oncologic possibilities. To this end, we will employ Carlson type 1, 2, 3 and 4 SSM [22] or NSM through an inframammary incision or vertical pattern.

*Reconstruction technique*. The reconstruction will be performed by placing a silicone implant coated with polyurethane foam (Microthane^TM^, POLYTECH Health & Aesthetics Dieburg, Germany. https://polytech-health-aesthetics.com) in the prepectoral position.

The authors confirm that all ongoing and related trials for this drug/intervention are registered.

### Modification and adherence

Does not apply to the type of study.

### Concomitant care

24-hour intravenous antibiotic prophylaxis is performed in all patients. Usually cefazolin. In patients allergic to penicillin, ciprofloxacin should be used.

### Outcomes

Primary outcome measures.

Incidence of implant loss (Feasibility of reconstruction). To evaluate the feasibility of prepectoral reconstruction in terms of implant loss the first year after surgery, also during oncological treatment (example: chemotherapy) (Unit of mesure: number of implant loss). Implant loss is defined as the need to remove the prosthesis for any cause such as strusion, infection or necrosis.

Secondary outcome measures.

Incidence of surgical complications—reoperations (Safety). To determine the global incidence of surgical complications, as well as the causes of complications in terms of: postoperative bleeding, skin necrosis, necrosis of the nipple areola complex, seroma and infection.
Postoperative bleeding is defined as the appearance of any amount of bleeding that modifies the course of the first 7 postoperative days. Among these modifications we find: the need to prolong admission due to blood drainage and the need for reoperation due to bleeding or hematoma. Superficial ecchymoses that do not modify the immediate postoperative period are not includedSkin necrosis is defined as the appearance of areas of skin without vascularization that condition cell death. Necrosis that appeared during the first 3 months after surgery that conditioned some action by the surgeon are included.Within the necrosis of the nipple areola complex, only deep necroses that required some surgical interventions are included.Seroma is defined as the accumulation of periprosthetic fluid that required maintaining the drain for more than 10 days or placing a new one (ultrasound-guided or at operating room).An infection is defined as the need for antibiotics in the first 30 postoperative days. The antibiotic prophylaxis used (Cefazolin the first 24 hours) is excluded.Incidence of residual glandular tissue (Safety). To evaluate the safety of sparing mastectomy through the identification of residual glandular tissue through a magnetic resonance one year after surgery.Incidence of breast cancer relapse (oncological safety). To evaluate the safety of sparing mastectomy through the identification relapses in the same breast during the follow up.Incidence of new breast cancer (safety of risk reducing mastectomy). To evaluate the safety of risk reducing sparing mastectomy in high risk for breast cancer patients through the identification of new breast cancer.Quality of life and satisfaction after a mastectomy with prepectoral reconstruction, using the Breast-Q questionnaire. To assess satisfaction and quality of life after prepectoral reconstruction in women with breast cancer and those with high risk through Breast-Q questionnaire. Also, to identify factors related to satisfaction and quality of life after prepectoral reconstruction (e.g. marital status, psychological illnesses).Incidence of cosmetic sequelae. To evaluate the cosmetic sequelae after prepectoral reconstruction in women with breast cancer and with high risk and Identify factors related to the cosmetic sequelae after prepectoral reconstruction. The investigators will employ the Clough classification, where type I sequelae identified the patients with breast asymmetry but no deformity, type II sequelae were defined by the presence of a deformity that could be corrected using a breast-conserving procedure, and type III sequelae identified those women whose breast showed a deformity or painful fibrosis that could only be solved through mastectomy. To determine the sequelae, the criteria of the breast surgeon will be used, documented through photos.

### Participants’ timeline (see Table 1 and Fig 1)

**Fig 1 pone.0269426.g001:**
[figure not shown]
Methodology algorithm for the PreQ-20 study.

**Table 1 pone.0269426.t001:** Schedule for patient assessment in the PreQ-20 study.

	STUDY PERIOD					
	Enrolment	Allocation	Post-allocation			Close-out
TIMEPOINT**	*-t* _ *1* _	0	*t* _ *1* _ _ *3 months* _	*t* _ *2* _ _ *1 year* _	*t* _ *3* _ _ *5 years* _	*t* _ *x* _
**ENROLMENT:**						
**Eligibility screen**	X					
**Informed consent**	X					
**MRI+ Picture + Breast Qpre**		X				
**Allocation/Inclusion**		X				
**INTERVENTIONS:**						
** *[Mastectomy and Prepectoral reconstruction]* **			X			
** *[Annual Control -MRI+ BreastQ post]* **				X		
** *[Long Term Follow up + BreastQ post]* **					X	
**ASSESSMENTS:**						
** *[List baseline variables]* **	X	X				
** *[List outcome variables]* **			X	X	X	X
** *[List other data variables]* **			X	X	X	X

MRI: magnetic resonance image

#### Preoperative assessment

All patients will be assessed by a surgeon of the unit who will indicate SSM/NSM and assess its feasibility for each patient. Similarly, the decision for the mastectomy will be made in consensus with the multidisciplinary committee. Before the surgery, the patients will undergo a mammography and magnetic resonance imaging to confirm the tumor size and rule out multifocality/multicentricity, as well as an evaluation of the distribution of glandular tissue and transitions between the breast and chest wall.

#### Breast magnetic resonance imaging

From the clinical standpoint, this diagnostic test is necessary for the follow-up of patients with breast reconstruction for the early diagnosis of relapses and deterioration of the breast implant. This study will employ the first magnetic resonance imaging during the postoperative period (between 12 and 18 months) to assess the residual glandular tissue following the mastectomy.

#### Breast-Q questionnaire

The Breast-Q questionnaire is aimed at evaluating patient-reported satisfaction and quality of life through the use of breast reconstruction modules. The questionnaires are the intellectual property of the University of Columbia (New York, USA), which freely allows their use for clinical research. The questionnaire is presented in 2 formats: the preoperative format, which is delivered to patients before the surgery, and the postoperative format, which is delivered to them 12–18 months after the surgery. Likewise, we will conduct a second postoperative assessment at 5 years of the surgery. The final score for each module will be calculated according to the Mapi Research Trust criteria [23] and will range from 0 to 100 (the higher the score, the greater the satisfaction and wellbeing).

#### Images

The evaluation of the cosmetic sequelae requires taking photographs of the patient’s chest (from the suprasternal notch to navel). Photographs will be taken prior to the surgery (frontal, right and left lateral), then again at 12–18 months and finally at 5 years of the surgery.

#### Follow-up

The initial follow-up of the patients will be performed by the surgeon. The immediate complications will be assessed during the first 24–48 h in the hospital (postoperative pain and bleeding). The patients will subsequently be followed in the doctor’s Breast Unit office. The first visits will be held at 1 week and at 15 days after the surgery. Visits will subsequently be scheduled at 1 and 3 months of the surgery. If there are any complications and/or incidences, an earlier visit will be scheduled.

The patients will visit the Medical Oncology and Radiation Oncology office to complete their adjuvant therapy. The oncology control tests will be performed according to the Breast Unit’s protocol, this includes a clinical review (surgeon or medical oncologist) every 3–6 months for the first 5 years. In these reviews, a directed physical examination and the corresponding imaging tests will be performed annually. During these consultations, data will be collected regarding local and systemic relapses.

The women at high risk will undergo annual check-ups in the Breast Unit office (surgeon). All study patients will be evaluated at 12–18 months after the surgery to undergo a breast MRI, imaging and to deliver the postoperative Breast-Q questionnaire. Those patients with RGT will be evaluated by surgeon. The decision to remove this tissue will be made between the patient and the surgeon, considering the amount of residual tissue, the vital status of the patient and the risk of a relapse or new tumor. Women with RGT who do not undergo a reoperation will be followed up with an annual ultrasound and / or MRI.

A second assessment will subsequently be conducted at 5 years during which new images will be taken and the postoperative Breast-Q questionnaire will be delivered.

### Sample size

According to the meta-analysis by Wagner et al. [1] and the iBRA study [21], the incidence rate of implant loss is 3.3% and 9%, respectively. Our study will therefore assume that a 5% loss of implants would be acceptable and will use this value for calculating the sample size. Therefore, with a 95% confidence level (95% CI), an accuracy of 5% and assuming a 10% of potential losses during follow-up, we estimated that the necessary sample size will be 81 patients.

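### The 5-point accuracy claimed for implant loss does not hold with about four expected events: at an observed 5% the upper 95% limit is about 12–13%, not 10%

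*Protocol article*

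**What the plan says.** The Sample size section of the protocol article cites two published implant-loss rates, 3.3% and 9%. It then decides to "assume that a 5% loss of implants would be acceptable and will use this value for calculating the sample size". The precision is fixed "with a 95% confidence level (95% CI), an accuracy of 5% and assuming a 10% of potential losses during follow-up", and the section concludes that "the necessary sample size will be 81 patients". It names no formula.

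The outcome concerned is the primary one: implant loss in the first year after surgery (Outcomes). The only hypothesis stated is that "Prepectoral breast reconstruction with polyurethane implant after mastectomy is a safe procedure" (Research hypothesis). The Statistical analysis section promises proportions with confidence intervals but names no interval method. It analyses surgical safety on the whole sample and leaves out patients with missing data.

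**The concern.** The sentence on accuracy is the only justification of the study's size, and it makes a definite promise: the implant-loss rate will be known to within 5 points at 95% confidence. At a rate of 5% in a sample this small, the number of losses is so low that a symmetric interval of plus or minus 5 points has its lower end at zero. A valid interval is asymmetric and extends further upwards.

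For a safety outcome the upper limit carries the information. A reader who takes the stated accuracy at face value would expect an observed 5% to rule out rates above 10%, and it would not.

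**Working it through.** **Inputs, all from the Sample size section.** Assumed rate p = 0.05; 95% confidence, so z = 1.96; accuracy d = 0.05, read as an absolute half-width; losses 10%; stated size 81. One outcome per woman is assumed throughout.

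**Reproducing 81.** Normal-approximation formula: n = z²p(1−p)/d² = 1.96² × 0.05 × 0.95 / 0.05² = 72.99, so 73 evaluable. For losses, 72.99/0.9 = 81.1, or 73 × 1.1 = 80.3, which rounds up to 81. (Rounding 73/0.9 up would give 82.) The stated size is reproduced, and the normal approximation is inferred from that match.

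**Expected events.** 73 × 0.05 = 3.65; if all 81 are evaluable, 81 × 0.05 = 4.05.

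**Wilson interval at p = 0.05, n = 73.** Limits = [p + z²/2n ± z√(p(1−p)/n + z²/4n²)] / (1 + z²/n).

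- z²/2n = 3.8416/146 = 0.0263, so the centre term is 0.0763.
- The root term is 1.96 × √(0.000651 + 0.000180) = 0.0565.
- The divisor is 1.0526.
- Limits: (0.0763 − 0.0565)/1.0526 = 1.9% and (0.0763 + 0.0565)/1.0526 = 12.6%.

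**95% limits by method (%).**

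| Evaluable | Losses | Normal approx. | Wilson | Exact (Clopper-Pearson) |
|---|---|---|---|---|
| 73 | 3.65 (5%, notional) | 0.00 to 10.00 | 1.88 to 12.62 | 1.27 to 12.78 |
| 73 | 3 (4.1%) | −0.44 to 8.66 | 1.41 to 11.40 | 0.86 to 11.54 |
| 73 | 4 (5.5%) | 0.26 to 10.70 | 2.15 to 13.26 | 1.51 to 13.44 |
| 81 | 4 (4.9%) | 0.22 to 9.66 | 1.94 to 12.02 | 1.36 to 12.16 |

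The first row is notional because 3.65 losses cannot be observed; the rows for 3 and 4 losses lie on either side of it.

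**Against the stated 5 points.**

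- 73 evaluable, observed 5%: average half-width (12.62 − 1.88)/2 = 5.4 (Wilson) and (12.78 − 1.27)/2 = 5.8 (exact). Upper arm 12.62 − 5 = 7.6 and 12.78 − 5 = 7.8.
- 4 of 81: average half-width (12.02 − 1.94)/2 = 5.0 and (12.16 − 1.36)/2 = 5.4. Upper arm 12.02 − 4.94 = 7.1 and 12.16 − 4.94 = 7.2.

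**Coverage if the normal-approximation interval were used.** Summing binomial probabilities at a true 5% over the counts whose interval contains 5% gives 88.2% (n = 73) and 91.0% (n = 81). At n = 73, the interval for 0 losses collapses to zero and that for 1 loss ends at 4.04%, so both lie wholly below 5%. Their joint probability is 0.0236 + 0.0909 = 11.5%. Misses in the other direction total 0.3%. The error is therefore almost all towards reassurance.

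**What the stated precision would need.** At an observed 5%, an average half-width of 5 points needs about 83 evaluable women (Wilson) or 94 (exact). An upper limit of 10% needs about 139 to 142.

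**The case against.** The strongest reply has four parts.

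*The calculation is conventional and correct.* This stands. A reader might infer that 81 is an arithmetic error; it is not. The fault lies in the precision attributed to it.

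*Accuracy in such a formula ordinarily means half-width, and on that measure the shortfall is small.* This also stands in part: 5.4 to 5.8 points with 73 evaluable, and about 5.0 by Wilson if all 81 are. But the planning formula implies a symmetric interval, and the departure from symmetry is large on the upper side even with 81.

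*The article does not say that a normal-approximation interval will be used in the analysis.* True, and the method may be set in a fuller document that is not shown. The coverage figures are therefore conditional. The statement of precision in the Sample size section does not depend on that choice.

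*The 9% rate is not a limit that the plan undertakes to exclude.* Correct. It is a published rate, cited on the way to choosing 5%. An observed 5% would not exclude it, but neither would the plan's own 5% plus or minus 5%, which reaches 10%. That follows in part from the precision chosen and not only from the approximation.

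A reader might also infer from the remark that "a 5% loss of implants would be acceptable" that an observed rate of 5% or less will be taken as proof of safety. The documents contain no such rule. They use 5% to calculate the size and promise a confidence interval with each proportion.

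**Conclusion.** The concern holds as a misstated precision. With 73 to 81 evaluable women, an implant-loss rate near 5% will carry an upper 95% limit of about 12 to 13%, against the 10% implied. The upper arm is about 7 to 8 points instead of 5; the average half-width falls short by at most 0.8 points. If a normal-approximation interval were used, its coverage at a true 5% would be 88% to 91% instead of 95%.

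This rests on three assumptions: accuracy means an absolute 5 points, each woman contributes one outcome, and between 73 and 81 women are evaluable. It does not show that 81 is miscalculated, that 9% is a declared threshold, or that the plan will judge safety on the point estimate. The stated figure should be corrected, but the point does not threaten the validity of the study, since any valid interval from the final data will show the true precision.

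**What to change.** Keep 81 patients and make three changes of wording.

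1. In Sample size, replace the accuracy claim with the precision that can be reached, for example: *With 73 to 81 evaluable women, an observed implant-loss rate near 5% has a 95% confidence interval (Wilson or exact) from about 1–2% up to about 12–13%.*
2. In Statistical analysis, use a Wilson or Clopper-Pearson interval for implant loss in place of the normal approximation.
3. State that the safety hypothesis will be interpreted with the upper confidence limit in view. It is fair to add that an observed 5% would not exclude the cited 9% rate.

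The cost is a less favourable precision statement. No patients, visits or procedures change. It is best done before the primary results are published.
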